## Data Storage and Security

All study computers and records will be stored in a secure room with access limited only to authorized staff. All computers and databases will be password-protected with limited access. Daily backup of the data will be done by a designated study staff onto an external hard drive and onto a server at the University of Washington. The external hard drive will be stored in a separate building that houses the data management center for the Research Care and Training Program in Kisumu (Director, [name]).

# STATISTICAL CONSIDERATIONS

## Sample Size Justification

We calculated the sample sizes for each specific aim using the methods described by Dupont WD et al. [27] using the following formula:

[figure not shown]

Where
[figure not shown]

n = desired sample size
Zα = standard normal deviate (z-score) corresponding to the 5% significance level (Zα = 1.96)
Zβ = standard normal deviate (z-score) corresponding to the acceptable type II error rate (Zβ = 1.28 for Objective 1; Zβ =0.84 for Objective 2)
p0 = probability of event in controls
p1 = probability of event among participants in the intervention arm, assuming the intervention works as hypothesized
m = number of control subjects per experimental subject

**Objective 1:** To determine the effect of regular, context-sensitive text messages sent to men after undergoing circumcision versus usual care on attendance of the scheduled 7-day post-operative clinic visit. We hypothesize that men who receive the SMS intervention will have higher rates of attendance compared to those receiving usual care.

Assuming that the proportion of men failing to return for the 7-day post-operative visit is 0.57 among the control group ([name], Nyanza Reproductive Health Society: personal communication), and a 2-sided test with a significance level of 0.05, with **600 men in each arm** we will have at least **90% power** to detect a relative risk between the two arms of **0.83** or larger.

**The following table summarizes the range of sample sizes required with different assumptions of the true relative risk of failure to return for subjects in the intervention arm relative to controls:**

|  | RR= 0.5 | RR= 0.6 | RR= 0.7 | RR= 0.8 | **RR = 0.83** | RR= 0.9 |
| --- | --- | --- | --- | --- | --- | --- |
| Sample Size (per arm) **90% power** | 61 | 98 | 177 | 402 | **557** | 1604 |
| Sample Size (per arm) **80% power** | 46 | 74 | 133 | 301 | 416 | 1199 |

**Objective 2:** To determine the proportion of men who resume sexual activity before 42 days post-procedure after receiving regular, context-sensitive text messages versus usual care within the 42 days post-circumcision. We hypothesize that men who receive the SMS intervention will report higher rates of abstinence from sex during the 42 days post-circumcision.

The proportion of circumcised men who reported early resumption of sexual activity in the South African MC trial was **0.225** [9]. This trial was selected because the counseling regimen used was designed to approximate programmatic implementation of MC. Assuming that the proportion of men resuming early sexual intercourse is 0.225 among the control group, a 2-sided test with a significance level of 0.05, beginning with 600 men in each arm and about 11% loss to follow-up at 42 days, with **532 men** remaining in each arm we will have at least **80% power** to detect a relative risk between the two arms of **0.70** or larger.

The following table summarizes the range of sample sizes required with different assumptions of the true relative risk of failure to return for subjects in the intervention arm relative to controls:

|  | RR = 0.50 | RR = 0.60 | RR = 0.65 | **RR = 0.70** | RR = 0.75 | RR = 0.80 |
| --- | --- | --- | --- | --- | --- | --- |
| Sample Size (per arm) **90% power** | 231 | 381 | 510 | 712 | 1048 | 1674 |
| Sample Size (per arm) **80% power** | 173 | 285 | 382 | **532** | 783 | 1251 |

[figure not shown]

Our enrollment target will therefore be1,200 participants (600 per arm).

## Statistical Analysis:

### Descriptive analyses

**Trial Profile**

The flow of participants through the study will be reported using a “CONSORT” diagram [28]. We will report the number of men screened, those who met inclusion criteria, those that were excluded and reasons for exclusion, and the number randomized by study arm. All participants for whom the primary outcomes will not be available will be reported as lost to follow-up.

**Baseline data:**

A table will be used to summarize the comparison of baseline characteristics for men in both study arms. This table will include descriptive statistics of the quantitative variables (mean, median, variance, range, IQR, standard deviations etc) as well as frequencies for the categorical variables. This table will serve to describe the study population, stratified by study arm, and also to verify that potential confounders were well balanced by randomization. Baseline characteristics that are not balanced between the study arms will be adjusted for in subsequent sub-group analyses. Baseline analyses will also analyze the extent and distribution of missing data.

Baseline characteristics that are continuous will be compared using Wilcoxon and t-tests. Characteristics that are categorical will be compared using Chi-square test. Analyses will be done using Stata (StataCorp. 2007. *Stata Statistical Software: Release 10*. College Station, TX: StataCorp LP.).

### Inferential analyses

The primary analysis will follow the intent-to-treat principle, that is, we will analyze the arm to which the subject was randomly assigned. All tests will be conducted at the 5% significance level (two-sided).

**Testable Hypothesis 1:**

A Chi-square test will be used to compare the proportions of men attending the scheduled 7-day post-operative visit by study arm. A follow-up analysis comparing the proportions attending 7-day visits will also be done that further adjusts for variables that were imbalanced between arms at baseline.

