### Sensitivity Analyses

Men who are not available for the 42-day assessment (lost to follow-up) will not be available for the analyses in objective 2. Baseline characteristics will be compared among those who are and are not lost to follow-up. Another comparison of baseline characteristics will be performed to assess imbalance between randomized groups among only those subjects who are not lost to follow-up; the analyses in objective 2 will be repeated analyzing for the imbalanced variables. Sensitivity analyses will also be performed that “impute” the missing data under various assumptions (e.g. missing as failure, multiple imputation).

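### The adjusted between-arm analyses choose their covariates by observed baseline imbalance rather than from a fixed prognostic list; the primary tests are not affected

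*Protocol*

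**What the plan says.** Section 10.2, Baseline data, plans a table by arm and attaches significance tests to it: "Baseline characteristics that are continuous will be compared using Wilcoxon and t-tests", with chi-square tests for categorical variables. It then sets a general rule: "Baseline characteristics that are not balanced between the study arms will be adjusted for in subsequent sub-group analyses".

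The rule recurs where the between-arm analyses are defined. Under Testable Hypothesis 1, the attendance comparison is followed by an analysis that "further adjusts for variables that were imbalanced between arms at baseline". Testable Hypothesis 2 repeats those words for the proportion resuming sex early and for time to resumption. Under Sensitivity Analyses, balance is assessed again among men not lost to follow-up, and "the analyses in objective 2 will be repeated analyzing for the imbalanced variables".

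The primary comparison for each objective is an unadjusted chi-square test by randomised arm. Section 6.2 lists the baseline data abstracted at enrolment, among them date of birth, education, employment, marital status and number of sex partners in the last month.

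**The concern.** Allocation is 1:1, in variable blocks and concealed in sealed envelopes (section 5.1). Differences between the full randomised arms are therefore chance, and a test of them cannot show which variables are worth adjusting for. A covariate is useful to the extent that it predicts the outcome. The rule can bring in an irrelevant variable that happens to differ and leave out a prognostic one that happens not to.

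The rule is also loosely fixed. Beyond the tests and the general 5% level, no criterion for imbalance is given. Continuous variables get both a Wilcoxon and a t-test, with nothing said about disagreement between them. Baseline data places the adjustment in sub-group analyses, whereas the hypothesis sections place it in follow-up comparisons of the whole arms.

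At stake is the planned check on both primary results. Nobody can say in advance which adjusted model will be reported, and a disagreement between adjusted and unadjusted results would be hard to interpret.

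**Working it through.** **1. The plan's own sample sizes (section 10.1).** Inputs: two-sided 5% level, 1:1 allocation, control rates 0.57 (Objective 1) and 0.225 (Objective 2), relative risks 0.83 and 0.70. The intervention rates are 0.57 × 0.83 = 0.4731 and 0.225 × 0.70 = 0.1575. With p̄ the mean of the two rates:

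n per arm = [z_α √(2p̄(1−p̄)) + z_β √(p0(1−p0) + p1(1−p1))]² / (p0 − p1)²

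- Objective 1, 90% power: 557, as stated. Power at 600 per arm is 92.0%.
- Objective 2, 80% power: 532, as stated. Power at 532 per arm is 80.0%, and 532/(1 − 0.11) = 598, consistent with 600.

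These figures belong to the unadjusted tests, so the covariate rule does not enter them.

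**2. How often chance flags a variable.** Section 6.2 lists 18 items. Without client number, phone number and date of circumcision, 15 remain. Assume that p < 0.05 defines imbalance, with one test per variable and independent variables:

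- P(at least one flagged) = 1 − 0.95^15 = 0.537
- Expected number flagged = 15 × 0.05 = 0.75
- Range: 40.1% for 10 variables, 64.2% for 20

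**3. What the rule does to the adjusted test.** A logistic simulation of Objective 1 used 600 per arm, 16 independent baseline variables and 4,000 runs per setting. Predictor strengths are assumptions, given as log odds ratios per SD. Power:

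| True predictors | Unadjusted | Imbalance-selected | Pre-specified predictors |
|---|---|---|---|
| 0.5 | 89.0% | 88.7% | 90.1% |
| 1.0 | 80.2% | 80.5% | 87.1% |
| 1.0, 0.5, 0.5 | 75.3% | 76.0% | 84.7% |

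The first-listed predictor was flagged in only about 5% of runs. Imbalance selection therefore performs much like no adjustment (at most about 1 point better), against gains of about 1 to 9 points from pre-specification. With no treatment effect, the imbalance-selected test rejected in 4.3 to 4.8% of runs, so no inflation appears. The treatment effect was held fixed as a conditional log odds ratio, which lowers unadjusted power below the planned 92%. The table compares strategies and does not give the trial's power.

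**4. Possible gain for Objective 2.** If fixed covariates explain a share v of outcome variance (assumed), the adjusted analysis behaves roughly as if n were 532/(1 − v):

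- v = 0.05: n = 560, power about 82%
- v = 0.10: n = 591, power about 84%
- v = 0.15: n = 626, power about 86%

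**The case against.** The strongest reply is that the rule governs only follow-up and sensitivity analyses. Nothing says that these replace the unadjusted primary tests. This stands, and it limits the point. A reader might infer that the primary error rates, power or sample size are compromised, or that the adjusted tests reject too often. The documents do not support the first, and the simulation does not support the second: the rule is inefficient and not reproducible, but it was not shown to be invalid.

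Four further replies have force.

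- The protocol never states that p < 0.05 defines imbalance, so the 54% is conditional on that reading. The tests are, however, the only method it gives.
- Nothing in the protocol shows that marital status, number of partners or age is a strong predictor. Finding predictors is a stated secondary objective, and a separate multivariable analysis of resumption is not tied to imbalance. The listed variables are plausible predictors, no more.
- The 82 to 86% belongs to the adjusted analysis only. At about 19% prevalence, a predictor with log odds ratio 0.5 per SD explains about 4% of variance, and one with 1.0 about 13%. The top of the range therefore needs very strong predictors.
- Among completers or early resumers, arm differences need not be chance, since both groups form after randomisation. Describing completers is a legitimate attrition check and should stay. Selecting covariates because they differ by arm is still a poor rule there, because the relevant ones predict outcome or missingness.

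A last reply is that the covariate list could be left to a statistical analysis plan. The exact list could be, but here the protocol itself fixes the selection rule, and a plan that follows it inherits the problem.

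**Conclusion.** The point holds for the follow-up adjusted comparisons of attendance, early resumption and time to resumption, and for the completer sensitivity analysis. Selection by imbalance ignores prognostic value and leaves the model to the data. In the full randomised set it would flag at least one chance difference in about 54% of trials, given a 5% criterion and 15 independent variables. The cost is precision and a predictable model in the supportive analyses: about 2 to 6 points of power for the adjusted Objective 2 analysis if covariates explain 5 to 15% of variance, which is an assumption. The 600 per arm and the primary conclusions do not depend on it. The separate multivariable analysis under Testable Hypothesis 2 is not stated to use the rule and is outside this point.

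**What to change.** - **Baseline data:** keep the table descriptive, drop the significance tests and delete the sentence that ties adjustment to imbalance.
- **Testable Hypotheses 1 and 2:** replace adjustment for imbalanced variables with one short list of plausible prognostic covariates from section 6.2. Fix it before outcome data are seen and use it whatever the observed balance. An example is age, marital status, number of sex partners in the last month, education and employment. Clinic is not among the items listed in section 6.2, so add it only if it is confirmed as recorded.
- **Reporting:** give the adjusted relative risk (for example from modified Poisson regression) beside the unadjusted chi-square result, and use the same list in the Cox model.
- **Sensitivity Analyses:** keep the completer comparison as a description of attrition. Adjust for the same fixed list, adding variables that predict outcome or missingness rather than those that differ by arm.

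The cost is a change of wording. The example list without clinic needs no new data, and the sample size and primary tests stay as they are.

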**Testable Hypothesis 2:**

A chi-square test will be used to compare the proportions of men resuming early sexual intercourse (defined as resuming sex before 42 days post-procedure) by study arm. A follow-up analysis comparing the proportions resuming early sexual intercourse will also be done that further adjusts for variables that were imbalanced between arms at baseline.

Among men who report early resumption of sexual intercourse, the time to resumption (in weeks from MC procedure to resumption) of sexual intercourse will be compared by study arm using Kaplan-Meier plots, log-rank tests, and Cox regression. A follow-up analysis comparing the time to resumption will also be done that further adjusts for variables that were imbalanced between arms at baseline.

We will also conduct a multivariable analysis to estimate the effect of resumption of sex as a function of several factors.

Among men who report early resumption of sexual intercourse, the number of sex partners (binary; 1 versus 2 or more) will be compared by study arm using a Chi-Square test. A relative risk and 95% confidence interval will be calculated.

Among men who report early resumption of sexual intercourse, the proportion of men reporting unprotected sexual intercourse will be compared by study arm using a Chi-Square test. A relative risk and 95% confidence interval will be calculated.

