## Specific Objectives

**Objective 1:** To determine the effect of regular, context-sensitive text messages sent to men after undergoing circumcision versus usual care on attendance of the scheduled 7-day post-operative clinic visit, in a randomized controlled trial.

**Hypothesis 1:** We hypothesize that men who receive the SMS intervention will have higher rates of attendance at the 7-day post-operative visit, compared to those receiving usual care.

**Objective 2:** To determine the proportion of men who resume sexual activity before 42 days post-procedure (wound healing is expected to be complete in the majority of circumcised men within 42 days [7]) after receiving regular, context-sensitive text messages versus usual care within the 42 days post-circumcision.

**Hypothesis 2a:** We hypothesize that men who receive the SMS intervention will report higher rates of abstinence from sex during the 42 days post-circumcision, compared to those receiving usual care.

**Hypothesis 2b:** We also hypothesize that, among those who resume sex before 42 days post-procedure, those who receive the messages resume sex later than those who do not.

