## Study Outcome Measures

### Primary Outcome Measures

The primary outcome measure for objective 1 is the proportion of men failing to return for a post-operative clinic visit at 7 days. This proportion will be determined by examining each participant’s clinic records after their 7th post-operative day. Adherence to this clinic visit will be analyzed as a dichotomous variable. Participants will be considered to have ‘attended’ or ‘not attended’ the clinic visit after the elapse of 3 days after the scheduled 7-day visit.

The primary outcome measure for objective 2 is the proportion of men who report resumption of sexual activity before 42 days post-circumcision. This proportion will be determined by self-report using a brief questionnaire delivered via SMS. The analysis will be as a dichotomous variable, with participants considered as having either ‘resumed’ or ‘not resumed.’ Among men who resume sex before 42 days post-circumcision, we will also compare the time to resumption by study arm.

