### Estimated value "dummy" calculations using predicted data values

| |  | **Fail to attend** | **Attend** | **Total** | | --- | --- | --- | --- | | SMS Group | 100 | 500 | 600 | | Control Group | 300 | 300 | 600 | | Total | 400 | 800 | 1200 | | RR = (100/600)  (300/600)  RR = 0.33  Conclusion: SMS reduces the risk of failure to attend clinic visits by 67% |
| --- | --- | --- | --- | --- | --- | --- | --- | --- | --- | --- | --- | --- | --- | --- | --- | --- | --- |

| |  | **Resumption** | **No Resumption** | **Total** | | --- | --- | --- | --- | | SMS Group | 95 | 505 | 600 | | Control Group | 135 | 465 | 600 | | Total | 400 | 800 | 1200 | | RR = (95/600)  (135/600)  RR = 0.70  Conclusion: SMS reduces the risk of early resumption of sex by 30% |
| --- | --- | --- | --- | --- | --- | --- | --- | --- | --- | --- | --- | --- | --- | --- | --- | --- | --- |

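### Time to resumption is compared only among men who resumed before day 42, a subset defined by the outcome that the messages are meant to change, so the comparison is not randomised and can miss or reverse a real delay

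*Protocol*

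**What the plan says.** Three places in the protocol agree with each other.

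- Specific Objectives, Hypothesis 2b, expects that "among those who resume sex before 42 days post-procedure, those who receive the messages resume sex later than those who do not".
- Primary Outcome Measures, after defining the 42-day proportion for Objective 2, adds: "Among men who resume sex before 42 days post-circumcision, we will also compare the time to resumption by study arm".
- Section 10.2, Testable Hypothesis 2, sets the analysis population and unit: "Among men who report early resumption of sexual intercourse, the time to resumption (in weeks from MC procedure to resumption"). The methods named are Kaplan-Meier plots, log-rank tests and Cox regression. A follow-up analysis adjusts for variables imbalanced at baseline.

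The Inferential analyses text states: "The primary analysis will follow the intent-to-treat principle, that is, we will analyze the arm to which the subject was randomly assigned". The sensitivity analyses address only men lost to follow-up. Nowhere does the protocol plan a time-to-resumption analysis of all randomised or all followed men.

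**The concern.** Whether a man enters this analysis is decided after randomisation, by the outcome that the intervention is meant to reduce. The protocol's own worked example concludes that "SMS reduces the risk of early resumption of sex by 30" per cent. If so, the SMS resumers are a smaller and differently selected group than the control resumers, and a difference in their timing mixes any delay with that selection. Adjusting for measured baseline imbalance cannot be relied on to undo it.

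The selection also works against the hypothesis. A man whom the messages carry past day 42 has the longest delay the trial can observe, yet he contributes nothing to the delay analysis. The trial could report no effect on timing, or an apparent hastening, for messages that do delay resumption.

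**Working it through.** **Inputs.** From Sample Size Justification: "Assuming that the proportion of men resuming early sexual intercourse is 0.225 among the control group"; relative risk 0.70, so 0.225 × 0.70 = 0.1575 on SMS; 532 men per arm after loss to follow-up. From Inferential analyses: "All tests will be conducted at the 5% significance level (two-sided"). Follow-up is 42 days. The protocol gives no distribution of resumption times and no power for this comparison, so every time distribution below is an assumption.

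**Step 1: reproduce the plan's figure.** With pooled variance and no continuity correction, n = [1.96·√(2p̄q̄) + 0.84·√(p0q0 + p1q1)]² / (p0 − p1)², where p̄ = 0.19125. This is (1.96 × 0.5562 + 0.84 × 0.5541)² / 0.0675² = 1.5556² / 0.004556 = 531.1, rounded up to 532. This agrees with the protocol.

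**Step 2: size of the subset.** Control: 532 × 0.225 = 119.7. SMS: 532 × 0.1575 = 83.8. The difference of about 36 men is the expected effect, and those men are absent from the timing comparison.

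**Step 3: what the subset shows, by arithmetic.** Take a constant control hazard. By day 21, 1 − √0.775 = 0.1197 of control men have resumed, which is 0.1197 / 0.225 = 53.2% of control resumers.

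- Proportional hazards on SMS: 1 − √0.8425 = 0.0821, and 0.0821 / 0.1575 = 52.1% of SMS resumers. The effect almost vanishes within the subset.
- SMS prevents only resumption after day 21: 0.1197 / 0.1575 = 76.0% of SMS resumers. They look much earlier than controls, although no man resumed sooner.

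**Step 4: analysis of all followed men.** HR = ln(0.8425) / ln(0.775) = 0.1714 / 0.2549 = 0.672, with about 203 events. Schoenfeld power is Φ(√203.5 / 2 × 0.397 − 1.96) = Φ(0.87) = 0.81.

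**Step 5: simulation.** 532 men per arm, 2,000 trials per scenario, times grouped by week, log-rank test, true 42-day relative risk 0.70 throughout. Shapes are Weibull; shape 1 is a constant hazard and higher shapes are rising hazards.

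| Assumed effect of SMS | Resumers-only HR | Resumers-only: SMS significantly later | Resumers-only: SMS significantly earlier | All men: favours SMS |
|---|---|---|---|---|
| Proportional hazards, shapes 1–5 | 0.96–0.98 | 3–4% | about 2% | 79–82% |
| Prevents only resumption after day 21, shape 1 | 1.73 | 0% | 81% | 74% |
| Same, after day 28, shape 2 | 1.65 | 0% | 72% | 74% |
| Same, after day 28, shape 3 | 1.43 | 0% | 40% | 75% |
| Same, after day 35, shape 3 | 2.21 | 0% | 96% | 74% |
| Lognormal times multiplied by 1.10–1.28 | 0.84–0.88 | about 10% | under 1% | 82–83% |
| Shift of 13.8 days, shape 1 | 0.52 | 95% | 0% | 87% |
| Shift of 3.2–7.6 days, shapes 2–5 | 0.73–0.84 | 10–35% | under 1% | 81–84% |

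Over a wider set of shapes and cut-offs for late prevention, the share of trials significantly favouring control ran from roughly 10% to 100%. It is lowest when the hazard rises steeply and the cut-off is early.

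**The case against.** The strongest reply is that the analysis matches Hypothesis 2b. Under proportional hazards, timing among resumers hardly differs, so a near-null result answers the question as worded. That stands as far as it goes: analysis and hypothesis are consistent. But the question is not one that randomisation protects, and a null answer to it would readily be read as no delay. The hypothesis therefore has to change along with the analysis.

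Second, the powered Objective 2 outcome is the 42-day proportion, tested by chi-square among all followed men. That is untouched, and men kept abstinent are counted there as benefit. The all-men log-rank has about the same power as the chi-square (81% against 80%), so the change adds little evidence on whether SMS works at all. This stands and limits the importance of the point. Even so, the timing comparison is a numbered hypothesis and sits under Primary Outcome Measures.

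Third, sign reversal needs messages that act mainly on late resumption, and the protocol gives no reason to expect that pattern over another. This also stands: reversal is a possibility, not a forecast.

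Three stronger readings are tempting, and the document supports none of them.

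- A reader might infer that Kaplan-Meier and Cox have no role because nobody in the subset is censored. Both remain valid without censoring; the fault is the subset.
- A reader might infer that times are recorded in whole weeks. The protocol gives weeks only as the analysis unit, the day-42 questionnaire is not shown, and the 7-day abstraction includes days since resumption.
- A reader might infer that a genuine delay always looks null. The constant-hazard shift, with 95% power, shows otherwise.

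Leaving the matter to a statistical analysis plan does not answer the point, because the protocol itself fixes the population.

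**Conclusion.** The concern holds in this form: the planned timing comparison conditions on a post-randomisation outcome that the intervention is expected to change, so it does not estimate the effect of SMS on time to resumption. At planning rates it compares about 120 control with 84 SMS men. With a true relative risk of 0.70, its power to show a delay ranged from nil to about 95% across the assumed mechanisms. It was 3–4% under proportional hazards, and a significant result in the wrong direction was possible when only late resumption was prevented. In the tabulated scenarios, analysing all followed men gave 74–87%.

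The non-comparability of the arms follows from the text alone. The sizes rest on the protocol's planning rates, on 532 followed men per arm, on weekly grouping and on time distributions that the protocol does not supply. Nothing here weakens the chi-square comparison of 42-day proportions.

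**What to change.** Reword Hypothesis 2b, the matching sentence under Primary Outcome Measures, and the time-to-resumption paragraph in section 10.2. Kaplan-Meier, log-rank and Cox should compare time from circumcision to first intercourse by randomised arm in all men with follow-up, censoring at day 42 those who have not resumed. Analyse time in days where the interview data allow. Keep timing among resumers as a descriptive summary, without a test or a causal reading. The comparisons of partner number and unprotected sex in the same section condition on the same subset and deserve the same caution.

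The cost is a change of wording in three places. It uses the same day-42 interview and needs no further participants.

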## Potential Benefits of Proposed Research to Study Subjects and Others

During the administration of the final questionnaire, participants will be invited to visit the clinic should they wish to receive free condoms.

Knowledge gained from this study will help inform policy makers and HIV prevention programs on devising strategies that can improve adherence to the 7-day post-op visit, reduce early resumption of intercourse after MC, and reduce the frequency of unprotected sexual intercourse.

This study will also provide critical information on the feasibility of using mobile telephony-based technology for public health interventions

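### Unprotected sex and number of partners are tested by arm only among men who resumed early, so if SMS works these two supporting comparisons are not protected by randomisation, and the direction of bias is unknown

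*Protocol*

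**What the plan says.** The Protocol, section 10.2, Testable Hypothesis 2, ends with two comparisons restricted to early resumers. For condom use: "Among men who report early resumption of sexual intercourse, the proportion of men reporting unprotected sexual intercourse will be compared by study arm". For partners, in the same group: "the number of sex partners (binary; 1 versus 2 or more) will be compared by study arm using a Chi-Square test". After each it adds: "A relative risk and 95% confidence interval will be calculated". Neither outcome is given a comparison over all assessed men anywhere in the protocol.

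The restricting event is itself an expected effect of treatment. Hypothesis 2a, under Specific Objectives, reads: "We hypothesize that men who receive the SMS intervention will report higher rates of abstinence from sex during the 42 days post-circumcision". Under Primary Outcome Measures, early resumption is the primary outcome for Objective 2.

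Two nearby statements do not change this. Intent-to-treat is stated for the primary analysis only: "The primary analysis will follow the intent-to-treat principle, that is, we will analyze the arm to which the subject was randomly assigned". The Sensitivity Analyses section deals with loss to follow-up and with baseline imbalance among retained men, not with selection into the resumer group.

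**The concern.** Randomisation makes the arms comparable as allocated. It does not make comparable two subgroups that are defined by something the treatment changes. If the messages stop some men from resuming early, those men stay in the control arm's resumer group and are absent from the SMS arm's. Where they differ in condom use or number of partners from men who resume regardless, the resumers-only RR mixes that difference with any effect of the messages on behaviour.

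At stake is how two reported results would be read. Section 8.5 says the findings should help programmes to "reduce the frequency of unprotected sexual intercourse". A chi-square test, RR and CI by arm will be taken as a treatment effect on that behaviour, and under the protocol's own hypothesis they would not be one.

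**Working it through.** **Inputs from the protocol (10.1, Objective 2).** Control rate of early resumption 0.225; RR 0.70, so the SMS rate is 0.225 × 0.70 = 0.1575; two-sided 5%; 80% power; 532 men per arm after about 11% loss from 600.

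**Reproducing the plan's figure.** Pooled-variance formula without continuity correction, mean proportion (0.225 + 0.1575)/2 = 0.19125:

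n = [1.96·√(2 × 0.19125 × 0.80875) + 0.84·√(0.225 × 0.775 + 0.1575 × 0.8425)]² / 0.0675²

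This gives 532 per arm, as stated. Loss is 1 − 532/600 = 11.3%.

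**Who enters the two tests.** Control: 532 × 0.225 = 119.7, about 120. SMS: 532 × 0.1575 = 83.8, about 84.

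**Composition of the control resumers.** Assume that SMS makes no man resume early who would otherwise have waited. The control resumers (0.225 of the arm) are then of two kinds:

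- men who resume regardless: 0.1575
- men SMS would have stopped: 0.225 − 0.1575 = 0.0675

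The second kind makes up 0.0675/0.225 = 30% of control resumers and is absent from the SMS resumers.

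**Effect on the RR.** The protocol gives no rate of unprotected sex, so the rates below are assumptions. Let u be the rate in men who resume regardless and v the rate in men SMS would stop, with no effect of SMS on condom use.

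- Control resumers: (0.1575u + 0.0675v)/0.225
- SMS resumers: u
- All assessed men: control 0.1575u + 0.0675v, SMS 0.1575u

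| | u = 60%, v = 40% | u = 50%, v = 80% |
| --- | --- | --- |
| Control resumers | (0.0945 + 0.0270)/0.225 = 54% | (0.07875 + 0.0540)/0.225 = 59% |
| SMS resumers | 60% | 50% |
| Planned (resumers-only) RR | 0.60/0.54 = 1.11 | 0.50/0.59 = 0.85 |
| All men, control vs SMS | 12.15% vs 9.45% | 13.28% vs 7.88% |
| All-men RR | 0.78 | 0.59 |

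In both columns SMS leaves condom use unchanged among men who resume regardless, so an unbiased RR in those men would be 1.00. The departures to 1.11 and 0.85 come from selection alone, in opposite directions. The same algebra applies to two or more partners.

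**Precision.** Take 50% unprotected in both resumer groups, giving 60 and 42 events.

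- Resumers only: SE(log RR) = √(1/60 − 1/120 + 1/42 − 1/84) = 0.14
- All assessed men: SE(log RR) = √(1/60 − 1/532 + 1/42 − 1/532) = 0.19

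**The case against.** **These analyses are peripheral.** Neither outcome appears among the objectives, hypotheses or listed outcome measures, and neither drives the sample size. The intent-to-treat statement covers the primary analysis, so it is not breached. This stands, and it limits the weight of the point.

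**The all-men point estimate can be recovered.** It is the product of two planned results, RR of resumption × RR among resumers (for example 0.70 × 1.11 = 0.78). That is true, but its confidence interval and test are not planned, and the result the protocol labels as the comparison by arm would still be the selected one.

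**Section 8.5 sets no estimand.** It is a general statement of benefit, and reading it as referring to all circumcised men is an interpretation. This stands. The argument rests on comparability and does not need that sentence.

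A reader might also infer three stronger claims that the documents do not support.

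- *That the plan would hide a benefit or show false harm.* The second column of the table shows selection producing an apparently favourable RR. The protocol has no data on which men SMS would stop, so the direction is unknown. Nor does equal condom use of 50% in all resumers show bias: the planned RR of 1.00 is then correct for resumers, and the all-men RR of 0.70 is the early-resumption effect already tested as a primary outcome. It answers a different question.
- *That the restriction wastes sample, about 204 men used instead of 1,064.* Abstainers add no events, and the resumers-only RR is the more precise of the two (0.14 against 0.19).
- *That the trial's randomised comparison is lost.* The primary test of early resumption by arm keeps all men assessed at day 42.

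**Conclusion.** The point holds for these two supporting comparisons and should be corrected. As written, each is a formal between-arm test in a group selected by the outcome that SMS is meant to change. The groups stay comparable only if SMS does not alter who resumes early, which would contradict Hypothesis 2a. At the planned effect, about 30% of control resumers have no counterpart in the SMS group, and modest assumed differences in condom use move the planned RR to 1.11 or 0.85 with no behavioural effect at all.

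The 30% rests on the planning rates and on SMS causing no man to resume early. The RRs rest in addition on assumed rates of unprotected sex and illustrate possible size; they are not predictions.

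**What to change.** In section 10.2, make the between-arm test for each outcome use all men assessed at day 42, by randomised arm:

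- any unprotected intercourse before day 42 (yes/no)
- two or more partners before day 42 (yes/no)

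Count men who did not resume before day 42 as no on both. Report the chi-square test, RR and 95% CI. Keep the resumers-only percentages by arm as description, without a p-value, and say that they are not a randomised comparison.

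This needs no further participants or visits and puts both outcomes on the same footing as the primary comparison of early resumption, including its dependence on loss to follow-up. There are two costs. The all-men RR has a somewhat wider interval. It also relies on the day-42 questionnaire asking about the period before day 42. That questionnaire is not shown and the call may come up to 7 days late, so the items should be checked before the wording is changed.
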